## Methods

### Aims of the trial

This study aims to test the effectiveness and cost-effectiveness of SOA and TOA against a waiting list control group, in a three-arm randomized clinical trial. Primary outcome measure is the change in alcohol consumption from baseline (t0) to the three month follow-up (t1) and to the six month follow-up (t2). Secondary outcome measures are changes in AUDIT scores, quality of life and quality of functioning at work. Incremental cost-effectiveness ratios for SOA and TOA will be calculated. The predictive validity of participant characteristics on treatment adherence and outcome will be explored.

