### Research questions

Q1a. Do TOA participants reduce their alcohol consumption from t0 to t1 and t2 to a larger extent than SOA and waiting list control participants?

Q1b. Do TOA participants improve to a larger extent on secondary outcome measurement scores from t0 to t1 and t2 than SOA and waiting list control participants?

Q1c. Are TOA participants more often treatment-responders than SOA and waiting list control participants at t1 and t2?

Q1d. Do SOA participants reduce their alcohol consumption to a larger extent from t0 to t1 and t2 than waiting list control participants?

Q1e. Do SOA participants improve on secondary outcome measurement scores from t0 to t1 and t2 to a larger extent than waiting list control participants?

Q1f. Are SOA participants more often treatment-responders than waiting list control participants at t1 and t2?

Q2. What are the comparative costs per quality adjusted life year (QALY) for SOA and TOA?

Q3a. How do participants' demographic characteristics relate to demographics of participants in conventional face-to-face CBT programs?

Q3b. Do scores of working alliance between TOA participants and counsellor predict treatment-response at t1 and t2?

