### Hypotheses

We hypothesize TOA participants will have reduced their alcohol consumption significantly more at the three month follow-up (t1) compared to SOA and waiting list control participants (Q1a). Between t0 and t1, we also expect TOA participants to improve on secondary outcome measurements (quality of life and working abilities) significantly more than SOA and waiting list control participants (Q1b). We hypothesize that a larger percentage of TOA participants will meet the criteria for treatment-responders compared to SOA and waiting list control participants (Q1c). We hypothesize that SOA participants will have reduced their t0 alcohol consumption significantly more at t1 than waiting list control participants (Q1d). Between t0 and t1, we also expect SOA participants to improve on secondary outcome measurements significantly more than waiting list control participants (Q1e). Finally, we hypothesize that a larger percentage of SOA participants will meet the criteria for treatment-responders compared to waiting list control participants (Q1f).

Between t1 and t2, we expect TOA participants to be better able than SOA participants to maintain their achieved changes in alcohol consumption, resulting in a significant time (t1–t2) by group (SOA-TOA) interaction. Alcohol consumption in SOA will be significantly higher at t2 compared to t1, whereas alcohol consumption in TOA will not change significantly during this period.

For question 2, we hypothesize that from t0 to t1 both the costs and the gains in QALY for SOA to be lower than the costs and the gains in QALY for TOA. As this means that both the numerator and the denominator of the cost-effectiveness equation is larger for TOA compared to SOA, we have no preconceptions of whether the incremental cost-effectiveness calculation will favour either SOA or TOA (Q2).

For question 3, we hypothesize our participants to be higher educated, a larger percentage to be working and female, compared to conventional outpatient SATC clients (Q3a). We also hypothesize that higher scores on working alliance will predict a larger proportion of treatment-response at t1 for TOA participants (Q3b).

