### Trial flow

Figure 1 provides an overview of the trial flow. If a participant is allocated to trial arm 1, he or she is directly introduced to TOA through a welcome text. A notification will now be sent to the TOA coordinator to make a first appointment for a chat session with the participant. From now on, TOA starts for participants in trial arm 1. Three months after t0 measurement, participants will receive an invitation for the t1 measurement by email and upon visiting the trial website. It is possible that some participants have not yet finished the entire TOA process after this period. However, the decision has been made to let follow-up timing depend solely on the time interval since t0, not on the current status of their treatment proceedings. This is in our opinion the best possible confirmation to the 'intention to treat' principle [40]. Three months after the t1 measurement participants are invited for the t2 measurement. After completion of t2 measurements, data collection is completed. Participants in trial arm 2 are introduced to SOA after randomization. Up until t1, participants can use the SOA program every time they log in on the trial website. t1 and t2 measurements are introduced by email and upon visiting the trial website. Participants in this trial arm are offered the possibility to proceed with TOA after completion of t2 measurements, would they be interested in more help after completion of SOA. Participants in trial arm 3 are allocated to the waiting list after randomization. After three months, they too will receive an invitation for the t1 measurement. After t1, participants in trial arm 3 are introduced to TOA. For ethical reasons, the decision is made to offer them TOA after three months (t1), and not after t2 (six months).

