### Data analysis

Multiple imputation missing data handling procedures will be implemented using MICE [45] a package for the R Statistical Software Environment. As the quantity of consumed alcoholic drinks is the primary outcome variable in this trial, analysis techniques are chosen that suit the expected data distribution. Baseline measurements of the three trial arms will be compared using t-tests and χ^2^-tests. Trial arm differences on primary and secondary outcome variables at three months are tested using repeated measures ANOVA. Trial arm differences for SOA and TOA between t1 and t2 are tested with a 2 (group) × 2 (time) repeated measures ANCOVA with between and within contrasts. Effect-sizes will be calculated using Cohen's *d *[46]. Trial arm differences on treatment-response will be tested using multiple logistic regression analysis. Costs from TOA and SOA will be derived from cost records of the collaborating SATC. Costs will be assessed in correspondence to the recommendations by the U.S. Panel on Cost-effectiveness in Health and Medicine [25], following a macro-costing approach. QALYs will be calculated from the EQ-5D questionnaire, using algorithm by Dolan [47], retrieved from the Open Health Measures website [48]. Based on these estimations, costs-per-QALY and an incremental cost-effectiveness ratio can be calculated. The U.S. Panel on Cost-effectiveness has recommended that cost-effectiveness studies should conduct sensitivity analysis, which for this cost-effectiveness analysis will be implemented through the bootstrap method [49-51].

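### For alcohol consumption, the plan states no TOA-versus-SOA contrast from t0 to t2, and the t1–t2 ANCOVA it names does not answer Q1a at six months as written

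*Protocol article*

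**What the plan says.** The section on the aims of the trial gives the outcome two horizons, both counted from baseline: "Primary outcome measure is the change in alcohol consumption from baseline (t0) to the three month follow-up (t1) and to the six month follow-up (t2". Q1a repeats both: "Do TOA participants reduce their alcohol consumption from t0 to t1 and t2 to a larger extent than SOA and waiting list control participants".

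The Data analysis section names two analyses of consumption:

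- For t1: "Trial arm differences on primary and secondary outcome variables at three months are tested using repeated measures ANOVA".
- For the later period: "Trial arm differences for SOA and TOA between t1 and t2 are tested with" a two-by-two (arm by visit) repeated measures ANCOVA, with contrasts both between and within arms. The covariate is not named.

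The Hypotheses section states TOA's superiority on consumption at t1 only. For t1 to t2 it predicts a significant interaction of visit with arm (SOA against TOA): consumption rises in SOA, "whereas alcohol consumption in TOA will not change significantly during this period".

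Two statements under Trial flow bear on what happens between t1 and t2. On SOA: "Up until t1, participants can use the SOA program every time they log in on the trial website". On TOA at three months: "It is possible that some participants have not yet finished the entire TOA process after this period". The waiting list is introduced to TOA after t1, while SOA participants are offered TOA only after t2.

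**The concern.** The outcome is defined from t0 to t2, but the only consumption analysis named for six months uses t1 and t2. Allocation follows the t0 measurement, so t1 is already affected by treatment. Change from t1 is therefore a different quantity from change since randomisation.

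The waiting list moves to TOA after t1, which leaves TOA versus SOA as the comparison without planned crossover at t2. If its t0–t2 contrast is not stated, the six-month part of Q1a for consumption has no declared answer. A reader would then have to rely on an interaction that can be null or reversed while TOA is better at six months, or on an average over two visits.

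**Working it through.** **The plan's own figure.** Table 3 gives N = 159 for a three-group one-way ANOVA with f = 0.25, α = 0.05 and power 0.80. With λ = N·f² = 159 × 0.0625 = 9.9375, critical F(2, 156) = 3.054 and noncentral-F power 0.8049, the stated 9.938, 3.054 and 0.805 reproduce. This is the only power figure given, and it covers none of the six-month contrasts below.

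**What each quantity estimates.** Let A1 and A2 be the mean advantage of TOA over SOA in consumption at t1 and t2 (positive means TOA drinks less). Randomisation makes the t0 means equal in expectation, so:

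- Q1a at six months: A2
- group-by-time interaction on t1 and t2: A2 − A1
- between-group effect on t1 and t2: (A1 + A2)/2

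Using t0 as covariate would improve precision but would not change these targets. The interaction is zero whenever A1 = A2, whatever their size. The between-group effect equals A2 only when A1 = A2.

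**Illustration in weekly units (invented values).**

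| Arm | t0 | t1 | t2 |
|---|---|---|---|
| TOA | 35 | 15 | 19 |
| SOA | 35 | 22 | 22 |

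- Reduction from t0 to t2: 35 − 19 = 16 against 35 − 22 = 13, so TOA is better by 3.
- Interaction: (19 − 15) − (22 − 22) = +4, which favours SOA by 4.
- Between-group effect: (15 + 19)/2 = 17 against (22 + 22)/2 = 22, which favours TOA by 5.

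The interaction favours the arm that is worse at t2. The averaged effect has the right sign but is not the six-month difference.

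**Power.** Inputs: n = 50 per arm (Randomization section), two-sided α = 0.05, equal SD at each visit, no dropout. The correlation ρ between visits is not in the document and is assumed to be 0.3, 0.5 or 0.7. In units of the visit SD, the SD of a change is √(2(1 − ρ)) and the SD after t0 adjustment is √(1 − ρ²). The noncentrality is (effect/SD)·√(n/2) = 5 × effect/SD. For example, an effect of 0.40 with ρ = 0.5 gives 5 × 0.40/1 = 2.00 for change and 5 × 0.40/0.866 = 2.31 for the adjusted value.

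| Stable advantage A1 = A2 | Contrast | ρ = 0.3 | ρ = 0.5 | ρ = 0.7 |
|---|---|---|---|---|
| 0.40 SD | t1–t2 interaction | 5% | 5% | 5% |
| 0.40 SD | t0–t2 change | 39% | 51% | 73% |
| 0.40 SD | t2 adjusted for t0 | 55% | 63% | 79% |
| 0.25 SD | t1–t2 interaction | 5% | 5% | 5% |
| 0.25 SD | t0–t2 change | 18% | 24% | 36% |
| 0.25 SD | t2 adjusted for t0 | 25% | 30% | 41% |

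**When the advantage is not stable.**

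- A1 = 0.60, A2 = 0.40: the interaction is −0.20, and its estimate favours SOA with probability 0.80, 0.84 or 0.90 as ρ rises, although TOA is better at t2.
- A1 = −0.40, A2 = 0: the interaction is +0.40 and is significant in TOA's favour in 39%, 51% or 73% of trials, with no difference at t2. The between-group effect is (−0.40 + 0)/2 = −0.20.
- A1 = 0.40, A2 = 0: the between-group effect is (0.40 + 0)/2 = 0.20, an apparent benefit when none is left at six months.

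**The case against.** The strongest reply is that the later analysis is more than an interaction test. It is an ANCOVA with between-arm contrasts. If t0 is the covariate, the between-group effect compares the arms on follow-up level and favours TOA in the illustration above. Under a stable benefit it estimates that benefit correctly, so the 5% applies to the interaction alone. The t2 contrast can also be recovered from the same model: (A1 + A2)/2 + (A2 − A1)/2 = A2. All of this stands. A reader might therefore be tempted to say that TOA and SOA are not compared on consumption at follow-up at all, and the text does not support that. What remains is that the covariate is unnamed, the averaged effect is not the t2 effect, and nothing says that a t2 contrast will be read. Detail may be left to an analysis plan that is not shown, but here the article does fix a six-month analysis, and it is aimed at a different quantity from the outcome the article declares.

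Three further inferences go too far:

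- *Six months is untested for every primary outcome.* Treatment response is also primary, Q1c asks about it at t1 and t2, and logistic regression is planned without restriction to t1.
- *The interaction was put in place of the primary comparison.* The Hypotheses section gives it a maintenance hypothesis of its own, which it answers properly; it is nowhere offered as the test of t0–t2 superiority.
- *Non-significant change in TOA is a success criterion.* The sentence is a prediction, and no decision rule is attached to it. The risk is only that a non-significant change with 50 participants is later read as stability.

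**Conclusion.** The point holds for alcohol consumption. The declared outcome includes change from t0 to t2, and the plan states no TOA-versus-SOA contrast for it. Neither effect of the named ANCOVA answers Q1a at six months: the interaction is zero for a stable benefit and can reverse sign, and the between-group effect mixes t1 with t2. These results are algebraic and need only randomised equality at t0.

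The power figures are illustrative. They rest on assumed correlations, equal SDs, approximate normality and complete follow-up; the weekly-unit example is invented.

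The three-month comparison and treatment response at t2 are unaffected. Continuing TOA after t1 is disclosed and follows from timing follow-up from t0. It limits how the t1–t2 contrast can be read as maintenance, but it is not an analysis error.

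**What to change.** 1. State TOA versus SOA consumption at t2, adjusted for t0, as the six-month primary comparison of consumption. Use either an ANCOVA of the t2 value on arm and t0, or a model with t1 and t2 as outcomes, t0 as covariate and an arm-by-time term, reading the t2 contrast. Name t0 as the covariate explicitly. The bootstrap and permutation methods that the Discussion reserves for non-normal data can be applied to this contrast.
2. Keep the t1–t2 interaction as a secondary analysis of maintenance, with a note that some TOA participants may still be in treatment after t1 while SOA use is described up to t1.
3. Report the within-TOA change from t1 to t2 with a 95% confidence interval, so that a non-significant result is not taken as evidence of stability.

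The cost is a few sentences in the analysis plan, settled before the follow-up data are analysed. The t0, t1 and t2 measurements are already scheduled, so no extra data or participants are needed for this change.

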### Measurement instruments

Several measurement instruments are included in the t0, t1 and t2 questionnaire, as presented in Table 2. Alcohol consumption will be measured using substance use subscales of the 'European Addiction Severity Index' (EuropASI) [15] and Timeline-Follow-Back for alcohol consumption [16]. This Timeline-Follow-Back method has good capacity to retrieve drinking history in the past week [17]. As a third scale to measure alcohol consumption burden the AUDIT is included [18].

**Table 2 T2:** Measurement instruments

**Instrument**	**t0 measure**	**t1 measure**	**t2 measure**
EuropASI (subscales)	x	x	x
Timeline-follow-back	x	x	x
AUDIT	x	x	x
QOL	x	x	x
EQ-5D	x	x	x
WAI-work	x	x	x
SF-HLQ	x	x	x
BSI	x	x	x
MCSDS	x		
Dutch mental health thermometer		x*	x*
WAI		x*	x*

Quality of life will be measured using two instruments: The EQ-5D [19-21] and the QOL [22]. The EQ-5D is a highly accepted, widely used and easy to administer instrument for measuring quality of life for alcohol and drug dependents [23,24]. As the scoring algorithm of the EQ-5D generates an index weighted by a preference measure, EQ-5D scores can be used in cost-effectiveness analysis to estimate QALYs [25]. However, it is recommended that the EQ-5D is used in combination with other quality of life instruments. This should be done to minimize its potential limitation in sensitivity until further results confirm EQ-5D validity in alcohol dependent individuals [26]. Therefore, the 'Quality Of Life' scale QOL [22] is included. According to content validity analysis, this is a valid instrument for measuring quality of life across patient groups and cultures. It is conceptually distinct from health status or other causal indicators of quality of life [27].

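### The article states no adjustment for baseline EQ-5D in the QALY difference behind the ICER, and leaves open how that difference is formed

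*Protocol article*

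**What the plan says.** The Data analysis section of the protocol article sets out the economic analysis as a chain. Programme costs come from the treatment centre's records. For effects, "QALYs will be calculated from the EQ-5D questionnaire, using algorithm by Dolan". Then "Based on these estimations, costs-per-QALY and an incremental cost-effectiveness ratio can be calculated". The last step is a sensitivity analysis, "which for this cost-effectiveness analysis will be implemented through the bootstrap method". No regression or covariate is named for the QALY difference.

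The only wording on which QALY quantity is meant stands in the Hypotheses section: "we hypothesize that from t0 to t1 both the costs and the gains in QALY for SOA to be lower" than those for TOA. This fits an area under the utility curve between t0 and t1, and it also fits a change from t0.

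The baseline score will be available. Under Measurement instruments, "Several measurement instruments are included in the t0, t1 and t2 questionnaire, as presented in Table 2", and that table marks the EQ-5D at all three times. The Randomization section places allocation after completion of t0, aims for 50 participants per arm, and accepts that chance may leave the arms unequal at baseline. Its remedy is adaptive allocation on factors that the article does not list.

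**The concern.** Treatment cannot affect the t0 utility, yet over t0-t1 that utility carries half the weight of an area under the curve. An arm that starts higher by chance is then credited with QALYs it did not produce. Subtracting t0 reverses the problem: through regression to the mean, the arm that starts higher tends to show the smaller gain. The two forms therefore give different ICERs from the same data, and neither removes the imbalance.

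The bootstrap does not help here. It shows the sampling spread around whichever estimate is computed and stays centred on that estimate, imbalance included.

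Cost-effectiveness is a stated aim of the trial. The ICER denominator is a small difference over a short horizon between two arms of about 50, so an avoidable shift or loss of precision in it matters for Q2.

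**Working it through.** **Plan's own figure.** The article gives no EQ-5D SD, no between-visit correlation and no precision for the ICER. Its sample-size table concerns alcohol consumption and does not bear on this point, so there is no figure to reproduce.

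**Inputs**
- From the article: n = 50 per arm (Randomization); t1 is three months after t0 (Trial flow).
- Assumed: equal EQ-5D SD s at each visit, with s = 0.20 for the absolute figures; t0-t1 correlation rho = 0.5, range 0.3 to 0.7; true TOA-SOA utility difference at t1 of 0.25 SD. The last figure is the d that the Power calculation section gives for alcohol consumption, borrowed here for the EQ-5D.

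**Step 1: the two possible QALYs over t0-t1 (0.25 year).** Let u0 and u1 be the utilities at t0 and t1.
- Area under the curve: A = 0.125(u0 + u1)
- Change from t0: G = A - 0.25·u0 = 0.125(u1 - u0)

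**Step 2: variance per participant, in units of 0.125²s².**
- Raw area: 2 + 2rho
- Change: 2 - 2rho
- Either one adjusted for u0: 1 - rho²

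The share removed by adjustment is (1 + rho)/2 against raw area and (1 - rho)/2 against change.

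| rho | raw area | change | adjusted | removed vs area | removed vs change |
|---|---|---|---|---|---|
| 0.3 | 2.60 | 1.40 | 0.91 | 65% | 35% |
| 0.5 | 3.00 | 1.00 | 0.75 | 75% | 25% |
| 0.7 | 3.40 | 0.60 | 0.51 | 85% | 15% |

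Over six months (weights 0.125, 0.25, 0.125, common correlation rho), the shares at rho 0.3 / 0.5 / 0.7 are 40% / 57% / 74% against raw area and 45% / 32% / 19% against change.

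**Step 3: what a chance imbalance does.** The SE of the t0 difference is 0.20 × sqrt(2/50) = 0.04. A t0 imbalance of that size also carries over into u1, by rho × 0.04 on average.
- Raw area: 0.125 × (1 + 0.5) × 0.04 = +0.0075 QALY (0.0065 at rho 0.3, 0.0085 at rho 0.7)
- Change: 0.125 × (0.5 - 1) × 0.04 = -0.0025 QALY (-0.0035 and -0.0015)
- Assumed true effect: 0.125 × 0.25 × 0.20 = 0.00625 QALY

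The ratio of shift to effect does not depend on the assumed SD. At rho 0.5 it is 0.0075/0.00625 = 1.2 for raw area and 0.0025/0.00625 = 0.4 for change.

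**Step 4: consequence for the sign of the denominator (s = 0.20, rho = 0.5).** The SE of the arm difference is 0.125 × 0.20 × sqrt(2/50) × sqrt(variance units) = 0.005 × sqrt(variance units).
- Raw area: 0.005 × sqrt(3.00) = 0.0087; effect/SE = 0.72; wrong sign about 24%
- Change: 0.005 × sqrt(1.00) = 0.0050; effect/SE = 1.25; about 11%
- Adjusted: 0.005 × sqrt(0.75) = 0.0043; effect/SE = 1.44; about 7%

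These chances use a normal approximation.

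**Step 5: does the choice of QALY form matter after adjustment?** A and G differ only by 0.25·u0. In a regression that contains u0, this moves the coefficient of u0 and leaves the arm coefficient unchanged. Over six months the difference is 0.5·u0, and the same holds.

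**The case against.** The strongest reply is that this is a condensed article. It names the utility source, the value set, the costing approach and the bootstrap, and it leaves the estimator open. A reader might infer that the trial has committed itself to a raw, unadjusted QALY difference. The text does not say so, and the full protocol or analysis plan may settle the matter. That stands, and the point is therefore limited to what follows if the article is applied as written.

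A reader might also infer that most of the available precision is lost. That holds for a raw three-month area under the curve. For a raw six-month area it needs a correlation above about 0.42. For three-month change from t0 it is not so, and the wording on gains makes that reading a natural one. On it, the carried imbalance is also smaller and runs the other way.

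Two safeguards might be cited. Adaptive allocation reduces imbalance on its chosen factors, but they are not listed, so the EQ-5D cannot be counted among them. The repeated measures ANOVA covers the EQ-5D as a secondary outcome, but nothing links it to the ICER.

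Finally, the SD, correlation and effect are all assumed, and no significance test of QALYs is planned. The first is conceded. Because of the second, the size is given here as variance, shift and sign of the denominator, not as power.

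**Conclusion.** The point holds as a free improvement and not as an error in a stated method. The article names no use of the t0 EQ-5D in the ICER denominator and leaves the form of the QALY open, and both forms it allows are inferior to the adjusted estimate at any correlation in the range considered.

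The size depends on which form is meant. It is large for raw area under the curve, where a one-standard-error imbalance can exceed the assumed effect. It is modest for change from t0. The percentages rest on equal SDs and the assumed correlation. The QALY figures rest also on the assumed SD and on an effect size borrowed from the alcohol outcome.

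**What to change.** In the Data analysis section, state that incremental QALYs will be estimated by regressing each participant's QALY on trial arm and t0 EQ-5D utility, and that the adjusted arm coefficient is the ICER denominator. Refit the regression within each bootstrap sample, so that the reported uncertainty belongs to the adjusted estimate. State the horizon and whether the QALY is an area under the curve or a change from t0, and report the unadjusted difference as a sensitivity analysis. The adjusted coefficient is the same under either definition, so this also ends the ambiguity for the main result.

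The cost is a sentence or two of analysis wording and one regression inside a bootstrap that is already planned. No new data are needed, because t0 is completed before allocation.
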